**Fig. 1 Fig1:**
[figure not shown]
Different scenarios as examples. Measurement numbers are based on the list above. Legend: Patient 1 has a treatment intervention within 6–8 h after hospital admission due to AMI. Blood sampling points will be on admission (M1), at the intervention (M3), 4–6 h after the intervention (M4), 12 h after the intervention (M5) and at reintervention (M7; if reintervention occurs within 72 h). Patient 2 has a treatment intervention later than 6–8 h after admission due to AMI. Blood sampling points will be on admission (M1), 6–8 h after M1 (M2), at the intervention (M3), 4–6 h after the intervention (M4) and 12 h after the intervention (M5). There was no re-intervention within 72 h. Patient 3 has suspicion of AMI while hospitalized and has no treatment intervention. Blood sampling points will be on suspicion of AMI (M1), 6–8 h after M1 (M2), 24 h after suspicion or diagnosis of AMI (M6) and 48 h after suspicion or diagnosis of AMI (M8)

#### Handling of blood samples and details of laboratory analytics

One lithium-heparin plasma tube (LH-tube) and one serum clot activator/gel tube (CA- tube) will be collected at each measurement point. Tubes will be centrifuged (10 min at 2000 g) no more than 2 h after blood collection and separated plasma/serum will be aliquoted to storage tubes. The samples will be stored at study sites at -80 °C and sent to the central laboratory in Tartu in two batches: one batch of samples at 4 months after the study start and the second batch after the end of the study.

Specific methods for biomarkers measurements are presented in Table 2.

**Table 2 Tab2:** Measurement methods of biomarkers

Biomarker	Rationale	Measurement	Data
**Enterocyte damage marker**			
I-FABP	Produced in small intestine (and colon?)	Plasma: LH-tube; Amount: 0.1–0.2 mL; Method: ELISA—Human FABP2/I-FABP Quantikine (DFBP20) Provider: R&D Systems (USA)	Moderate accuracy in humans (4); not IVD-R compatible
**Intestinal barrier dysfunction markers**			
D-lactate	Produced by intestinal microflora	Plasma: LH-tube; Amount: 0.2 mL Method: colorimetric—D-Lactate Assay Kit (MAK336) Provider: Sigma Aldrich (Germany)	Low accuracy in humans (4). Animal studies: fast peak (6 h), increase with reperfusion; not IVD-R compatible
LPS-binding protein	Increased production if more endotoxins with portal blood to liver	Plasma: LH-tube Amount: 0.1–0.2 mL Method: Human LBP DuoSet ELISA (DY870-05) Provider: R&D Systems (USA)	No data in humans in AMI; not IVD-R compatible
**Tissue ischaemia marker**			
IMA	Ischaemia-marker, not tissue-specific	Serum: CA-tube Amount: 0.1–0.2 ml Method: human IMA ELISA (CSB-E09594h) Provider: Cusabio (China)	Moderate accuracy in humans (4). Animal studies: Fast peak (6 h); not IVD-R compatible
**Inflammatory markers**			
IL-6	Inflammatory marker (not tissue-specific)	Plasma: LH-tube Amount: 0.2 mL Method: Cobas ECLIA; Provider: Roche Diagnostics, Germany) Reference value: < 7 ng/L	Moderate accuracy in humans (4). Animals: fast peak (6 h), increase with reperfusion; IVD-R compatible
PCT	Inflammatory marker (not tissue-specific)	Plasma: LH-tube Amount: 0.2 mL Method: Cobas ECLIA; Provider: Roche Diagnostics, Germany) Reference value: < 0,5 µg/L	Moderate accuracy in humans (4); IVD-R compatible
**Thrombosis/coagulation markers**			
D-dimer	Activation of coagulation (any, not specific to AMI)	Plasma: LH-tube Amount: 0.2 mL Method: Cobas ECLIA; Provider: Roche Diagnostics, Germany) Reference value: < 0.5 mg/L	Moderate accuracy for transmural AMI in humans; IVD-R compatible
SCUBE-1	Activation of coagulation Early marker of thrombosis (any)	Serum: CA-tube Amount: 0.1–0.2 mL Method: Human SCUBE1 ELISA kit (CSB-E15005h) Provider: Cusabio (China)	Not studied in humans. Animals: Peak 6 h? Small increase with reperfusion; not IVD-R compatible
**Other**			
Alpha-GST	A marker of liver injury	Serum: CA-tube Amount: 0.1–0.2 mL Method: Human α-GST ELISA Kit (CSB-E08906h) Provider: Cusabio (China)	Low accuracy in humans (4), no studies on transmural; not IVD-R compatible

*alpha-GST* Alpha- glutathione S-transferase, *CA-tube* Clot activator containing tube with gel, *ECLIA* Electrochemiluminescence immunoassay, *ELISA* Enzyme-linked immunosorbent assay, *IL-6* Interleukin-6, *I-FABP* Intestinal fatty acid-binding protein, *IMA* Ischaemia modified albumin, *IVD-R* In-Vitro Diagnostic Regulation 2017/746, *LH-tube* Lithium-heparin containing plasma tube, *LPS* Lipopolysaccharide, *SCUBE-1* Signal peptide-CUB-EGF domain-containing protein 1

### Data collection

Demographic data, chronic and acute health conditions, times from beginning of symptoms to treatment and diagnosis, details of AMI diagnosis, subtype and management, histology data (if available), and outcome data will be collected (Additional File 1).

### Statistical analysis

#### Sample size

The estimated sample size is in total of 250 patients, 160 patients with confirmed AMI (including 40 patients with NOMI) and 90 patients with suspected but not confirmed AMI.

In the AMESI study, European and West-Asian sites recruited 14 patients with confirmed AMI in average (range 3–34) and 7 (range 0–25) with suspected but eventually not confirmed AMI per site during 10 months. Accordingly, 20 sites are expected to encounter 220 patients with confirmed AMI and 120 patients with suspected AMI during 8 months. Estimating 5% of patients allocated to palliative treatment without any further diagnostics, 10% of referrals and 15% of patients being excluded for other reasons (e.g. missing informed consent, logistical reasons), 20 sites recruiting patients during 8–10 months are necessary to reach the targeted number of patients. As the number of patients with suspected AMI and confirmed NOMI is difficult to predict, the final decision regarding recruitment period will be made after the interim analysis after 4 months of the study.

Statistical analysis will be performed with R Statistical Software 4.3.2 (R Core Team, Vienna, Austria, 2023). Data will be described in number (%), median (interquartile range, IQR) or mean (standard deviation, SD) as appropriate. Kolmogorov–Smirnov test will be used for data distribution normality testing. Analyses for confirmed transmural AMI vs suspected but not confirmed AMI (comparison A – primary outcome), confirmed AMI of any stage vs suspected but not confirmed AMI (comparison B – secondary outcome) and transmural vs non-transmural AMI (comparison C – secondary outcome) will be performed in different measurement time points. Each biomarker will be described at each measurement point for all comparisons (A, B and C), using Student’s t-test or Wilcoxon rank-sum test as appropriate. For all biomarkers showing a *p*-value < 0.05 in at least one measurement point in univariate analysis, the area under the receiver operating curve (ROC) calculation will be performed. We will do this separately for comparisons A, B and C and identify optimal cut-off values for each biomarker based on maximum value of the Youden index [13]. All measurement time points before any treatment of AMI (1,2,3,6,8) will be pooled and AUROC analysis will be performed to identify the best cut-offs also for pooled data for each biomarker. Sensitivity, specificity, positive predictive value (PPV), negative predictive value (NPV) and likelihood ratios (LR) with 95% CI-s will be reported. Positive likelihood ratio (LR +) > 10 and negative likelihood ratio (LR-) < 0.1 will be considered high diagnostic accuracy and LR +  > 5 and LR- < 0.2 as moderate diagnostic accuracy. All biomarkers with at least moderate accuracy will be entered as binary covariates (using the best cut-offs previously found in the AUROC analyses resulting in highest AUC) into the multivariable stepwise logistic regression analysis (both directions) to identify the best combination of biomarkers discriminating between transmural AMI and no AMI based on Akaike information criterion (AIC). Analogical approach will be used for comparisons B and C. The best models will be applied to subgroup analyses in different sub-types of AMI. If the best models selected as described previously, do not perform well at different measurement time points or in different subtypes of AMI, additional analyses will be undertaken testing alternative combinations. We will present the best models for each comparison and for each subtype separately and will use them to construct a practical score that can be used to distinguish between no AMI, non-transmural AMI and transmural AMI (Table 3). If the different cut-offs from different models contradict (for example cut-off for non-transmural AMI vs transmural AMI is lower than the cutoff for no AMI vs AMI) additional analyses will be performed and more appropriate cut-offs will be found considering acceptable sensitivity and specificity from previous AUROC analyses. This approach will be compared to decision tree approach and if the decision tree accuracy is higher than the score’s accuracy, a decision tree will be preferred. The accuracy of the decision tree and the score will be calculated as proportion of correct predictions.

**Table 3 Tab3:** Hypothetical visualization of a practical score for diagnosis of AMI

	No AMI	Non-transmural AMI	Transmural AMI
Biomarker 1	< x = 0 points	x–y = 1 point	> y = 2 points
Biomarker 2	< x = 0 points		> x = 2 points
Biomarker 3	< x = 0 points	x–y = 1 point	> y = 2 points
Biomarker 4	< x = 0 points	> x = 1 point	
Biomarker 5	< x = 0 points		> x = 2 points

This visualization is hypothetical. PPV – positive predictive value

Hypothetical examples: 0–1 points = no AMI (PPV; 2–4 points = non-transmural AMI (PPV); > 5 points = transmural AMI (PPV)

Dynamics of each biomarker will be visualized graphically in patients with confirmed AMI differentiating between patients in whom initial treatment was successful from patients in whom bowel ischaemia was ongoing after initial treatment, with the aim to explore possible differences in biomarker trajectories in case of reperfusion and ongoing bowel ischaemia.

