**Methods:**

This is a prospective multicentre study. Adult patients with clinical suspicion of AMI (*n* = 250) will be included. Blood will be sampled on admission, at and after interventions, or during the first 48 h of suspicion of AMI if no intervention undertaken. Samples will be collected and the following serum or plasma biomarkers measured at Tartu University Hospital laboratory: intestinal fatty acid-binding protein (I-FABP), alpha-glutathione S-transferase (Alpha- GST), interleukin 6 (IL-6), procalcitonin (PCT), ischaemia-modified albumin (IMA), D-lactate, D-dimer, signal peptide-CUB-EGF domain-containing protein 1 (SCUBE-1) and lipopolysaccharide-binding protein (LBP). Additionally, more common laboratory markers will be measured in routine clinical practice at study sites.

Diagnosis of AMI will be confirmed by computed tomography angiography, surgery, endoscopy or autopsy.

Student’s t or Wilcoxon rank tests will be used for comparisons between transmural vs. suspected (but not confirmed) AMI (comparison A), confirmed AMI of any stage vs suspected AMI (comparison B) and non-transmural AMI vs transmural AMI (comparison C). Optimal cut-off values for each comparison will be identified based on the AUROC analysis and likelihood ratios calculated. Positive likelihood ratio > 10 (> 5) and negative likelihood ratio < 0.1 (< 0.2) indicate high (moderate) diagnostic accuracy, respectively. All biomarkers with at least moderate accuracy will be entered as binary covariates (using the best cutoffs) into the multivariable stepwise regression analysis to identify the best combination of biomarkers for all comparisons separately. The best models for each comparison will be used to construct a practical score to distinguish between no AMI, non-transmural AMI and transmural AMI.

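### Selecting Student's t or Wilcoxon after a Kolmogorov–Smirnov pre-test can, under mild skew or in small cells with unequal spread, make the p < 0.05 screen test something other than the AUC that follows; the rank-sum test throughout is a cheap, minor improvement

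*Protocol article*

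**What the plan says.** In the protocol article, Methods, Statistical analysis (the text after the sample-size paragraphs), three sentences bear on this point:

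- Normality: "Kolmogorov–Smirnov test will be used for data distribution normality testing".
- Group comparison: every marker is compared at every time point, in A, B and C alike, "using Student’s t-test or Wilcoxon rank-sum test as appropriate".
- Screen: the next step is selective. It applies "For all biomarkers showing a *p*-value < 0.05 in at least one measurement point in univariate analysis"; only for these markers are an ROC curve and its area obtained, again per comparison.

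The abstract names the same pair of tests: "Student’s t or Wilcoxon rank tests will be used for comparisons between transmural vs. suspected (but not confirmed) AMI (comparison A" and likewise for B and C.

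A marker enters the multivariable model only if it reaches at least moderate accuracy at its best cut-off, that is LR+ above 5 and LR− below 0.2.

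The text does not state whether the Kolmogorov–Smirnov (KS) test uses estimated parameters, whether a Lilliefors correction applies, or whether it is run per group or on pooled values. Nor does it say outright that the KS result alone decides between the two tests. It gives no SD or distribution for any biomarker.

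**The concern.** The standard KS reference distribution assumes a normal curve whose mean and SD are fixed in advance. The protocol gives no such values, so the natural implementation takes both from the sample. Without a correction the test then rejects far too rarely, and a non-significant result is read as normality.

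The two candidate tests also answer different questions. The screen decides which markers go on to AUC analysis, so the relevant null is no discrimination, AUC = 0.5. The rank-sum statistic, divided by the number of pairs, is the empirical AUC. Student's t compares raw means. For a right-skewed concentration whose spread differs between groups, the means can differ although AUC is 0.5.

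At stake are the univariate p-values reported for A, B and C and the list of markers that reach ROC analysis. The test used for one marker could also change from one time point to the next, partly because the number of patients changes.

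**Working it through.** **Inputs from the protocol.** Sample size: "160 patients with confirmed AMI (including 40 patients with NOMI) and 90 patients with suspected but not confirmed AMI", and 160 + 90 = 250, which agrees with the stated total. These are the group sizes for comparison B. The threshold is p < 0.05, taken as two-sided. The protocol states no power or error rate for the screen, so there is no figure of its own to reproduce for that step.

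**Assumptions, none of them in the protocol.** Markers are log-normal with equal medians in both groups, so AUC = 0.5; log-SD runs from 0.25 to 1.5. Comparison A is taken as 80 vs 90 (half of confirmed AMI transmural). Smaller cells stand for time points such as M6 and M8, which Table 1 restricts to patients without intervention and, if AMI is unconfirmed, to those still under suspicion. Rule simulated: KS in each group with sample mean and SD and the standard critical value; Student's t if neither group rejects, Wilcoxon otherwise. 3,000 to 10,000 runs per setting.

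**Step 1: how often KS rejects, per group.** Truly normal data: at most 0.02%, against 5% nominal. Log-normal data:

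| n | log-SD 0.5 | 0.75 | 1.0 |
|---|---|---|---|
| 20 | 1% | 7% | 20% |
| 40 | 7% | about 33% | about 64% |
| 90 | 35% | 86% | 99% |
| 160 | 77% | 100% | 100% |

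With the Lilliefors critical value, detection rises from 32% to 89% at n = 40 and log-SD 0.75, and from 29% to 90% at n = 80 and log-SD 0.5.

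**Step 2: why the t-test can reject at AUC 0.5.** A log-normal marker with median 1 has mean exp(σ²/2). For log-SDs 0.5 and 0.3 the ratio of means is exp((0.25 − 0.09)/2) = exp(0.08) ≈ 1.08. For 1.0 and 0.5 it is exp((1 − 0.25)/2) = exp(0.375) ≈ 1.45. The medians are equal, so AUC stays at 0.5.

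**Step 3: share of AUC-0.5 markers declared significant.** Ranges show the spread over repeated simulations.

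| Group sizes | log-SDs | KS-led choice | Wilcoxon only |
|---|---|---|---|
| 20 / 40 | 1.0 / 0.5 | 25–27% | 8–9% |
| 40 / 40 | 1.0 / 0.5 | 14% | 6% |
| 60 / 90 | 0.75 / 0.4 | 19% | 7–8% |
| 80 / 90 | 0.5 / 0.3 | 16–17% | 6–7% |
| 80 / 90 | 0.75 / 0.4 | 11–12% | 6% |
| 80 / 90 | 1.0 / 0.5 | 8% | 7% |
| 160 / 90 | 0.3 / 0.5 | 21% | 7% |
| 160 / 90 | 0.75 / 0.4 | 3.6% | 3.6% |
| 160 / 90 | 1.0 / 0.5 | 4.2% | 4.2% |

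The direction of the imbalance matters: at 160 / 90, swapping 0.3 / 0.5 for 0.5 / 0.3 lowers the KS-led rate from 21% to 7%.

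**Step 4: conditions under which the excess disappears.** With the same distribution in both groups, the KS-led rule rejects 4.0–5.9% across sizes. With KS on pooled values, rates are 3.4–8.3% at 80 / 90 and 160 / 90, and about 9% instead of 26% at 20 / 40.

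**Step 5: the opposite error.** With equal log-SD 1.0, AUC 0.75 and 15 per group, the screen's power is 59% under the KS-led rule and 67% with Wilcoxon. At about 80 vs 90 with equal spread the two are nearly the same.

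**Step 6: what reaches the model.** The probability that an AUC-0.5 marker meets LR+ > 5 and LR− < 0.2 at its Youden cut-off was 0.000 at 80 / 90 and at most 0.0002 at 15 / 15.

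**The case against.** A reader might infer that KS almost never rejects, that skewed biomarkers therefore generally go to the t-test, and that useless markers pass at two to three times the nominal rate. The protocol and the calculations do not support that.

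- The near-zero rejection rate belongs to normal data. Markers with log-SD 0.75 or more are detected in 86–100% of groups of 90 to 160 and go to Wilcoxon.
- Skew alone does no harm. The excess needs unequal spread together with mild skew or few patients, and every spread used here is assumed.
- The implementation is a reading of the text. Lilliefors-corrected or pooled testing would remove much of the problem, and such detail may sit in an analysis plan that is not shown. KS run against a standard normal with no parameters supplied rejected every positive marker tried, which would always lead to Wilcoxon.
- The equal-variance assumption is not the main cause at 80 / 90: Welch's t on raw values rejects at a similar rate (0.183 against 0.208), because the means truly differ. The t-test is then right about its own null. In small unbalanced cells pooling the variance does add to the effect (15 / 30, log-SDs 1.0 / 0.5: Student 0.233, Welch 0.060).
- The primary objective is defined by the likelihood ratios of a combination. AUC-0.5 markers do not get that far, and their AUC would be reported beside the p-value.

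All of this stands, and it limits the point to a conditional and minor one. It does not remove it. The article itself names the normality test and both comparison tests and offers no other criterion for choosing between them. How KS is run, which is left open, moves the error rate from about 26% to 9% in the 20 / 40 example.

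**Conclusion.** The point holds as a conditional, minor one. If KS is run per group with estimated parameters and no correction, if skew is mild or the cell is small, and if spread differs between groups, then a marker with AUC 0.5 can be declared significant in roughly 10–25% of studies, against 5–8% with Wilcoxon. Outside those conditions the rate is about nominal or close to Wilcoxon's, so no general inflation factor should be claimed. The figures rest on assumed log-normal markers, assumed log-SDs, an assumed transmural share and assumed cell sizes. The consequence is confined to the reported univariate p-values and the list of markers taken to ROC analysis; the multivariable models and the primary objective are in practice protected by the likelihood-ratio condition. Wilcoxon is not exact under unequal spread either (2.6–8.6% over all sizes tried), but it tests the quantity that the next step estimates.

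**What to change.** In the Statistical analysis section, delete the Kolmogorov–Smirnov sentence and state that every biomarker, at every time point and in comparisons A, B and C, is compared with the Wilcoxon rank-sum test and summarised by median (IQR). Change the abstract's description of the tests to match. If a parametric comparison is also wanted, name in advance a Welch t-test on log-transformed values, not selected by a normality test.

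The cost is two sentences of wording, with no new data and less analysis work. The only statistical price is about 5% lower efficiency for any marker that is truly normal with equal variances.

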#### Blood sampling time points

Two sampling tubes (one serum and one plasma, arterial or venous) will be collected at each measurement point, allowing central measurement of aforementioned biomarkers.

Depending on whether AMI is confirmed or not, and on treatment methods applied, different measurement time points will apply for each patient (Table 1 and Fig. 1).

**Table 1 Tab1:** Sampling time points for biomarkers measurements (M)

M no	Time point for blood sampling	Confirmed AMI with intervention	Suspicion of AMI*	Confirmed AMI without intervention
M1	Admission (suspicion, if in-hospital)	x	x	x
M2	6-8 h after the first sample if no intervention performed by then	x (if no intervention before 6-8 h)	x	x
M3	At intervention	x (incl. i/a vasodilation)		
M4	4–6 h after intervention	x		
M5	12 h after intervention	x		
M6	24 h after the first sample if no intervention		x (if suspicion still actual)	x
M7	At the time of re-intervention	x (if any within 72 h)		
M8	48 h after the first sample		x (if suspicion still actual)	x (if no intervention)

* If the case is confirmed, the patient will be moved to either column “Confirmed AMI with intervention” or “Confirmed AMI without intervention”

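### Time-point AUROC and likelihood ratios are calculated only for biomarkers that reach an unadjusted p < 0.05 at some time point, so single-marker accuracy is reported selectively

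*Protocol article*

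**What the plan says.** All of this is in the Protocol article, Methods, Statistical analysis (the text under the Sample size heading), unless another section is named.

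- Univariate step: "Each biomarker will be described at each measurement point for all comparisons (A, B and C), using Student’s t-test or Wilcoxon rank-sum test as appropriate".
- Filter: the condition that a marker must meet is "For all biomarkers showing a *p*-value < 0.05 in at least one measurement point in univariate analysis". The step to which this admits it is stated directly afterwards, namely that "the area under the receiver operating curve (ROC) calculation will be performed". The rule is applied per comparison: "We will do this separately for comparisons A, B and C". No adjustment across time points or markers is stated.
- What follows from it: Youden cut-offs, then sensitivity, specificity, predictive values and likelihood ratios with 95% confidence intervals.
- Pooled step: "All measurement time points before any treatment of AMI (1,2,3,6,8) will be pooled", with an AUROC analysis to find pooled cut-offs for each marker. This sentence neither repeats the p-value condition nor lifts it.
- Model gate: only markers with at least moderate accuracy (LR+ > 5 and LR- < 0.2) go into the stepwise logistic regression.
- Blood sampling time points: "Depending on whether AMI is confirmed or not, and on treatment methods applied, different measurement time points will apply for each patient". Table 1 schedules no M3, M4, M5 or M7 sample for patients whose AMI is only suspected.
- Objectives: the primary and both secondary objectives concern accuracy at one or more time points before any treatment of AMI.

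**The concern.** The rule makes a significance test decide which markers get an accuracy estimate. Three things follow.

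1. A marker that fails at every point is left with group summaries and p-values, but with no time-point AUROC or likelihood ratio and no interval around them. The Background and Discussion argue that earlier biomarker studies do not settle which markers are useful. An estimate with a confidence interval for a poor marker is what would settle it. The Discussion also calls the risk of finding no accurate combination considerable. If that happens, the single-marker estimates become a main product of the study.
2. AUROCs that are shown because they were significant are too high on average when the marker is weak.
3. The filter is not confined to the time points that the objectives concern. In comparison C both groups have confirmed AMI, so a marker can qualify on a sample taken after an intervention (M4, M5 or M7).

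**Working it through.** The protocol gives no pass rate or error rate for this filter, so there is no figure of its own to reproduce.

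**Inputs from the protocol.** The threshold is p < 0.05 (sidedness not stated; taken as two-sided). Comparisons A and B can be tested at 4 points (M1, M2, M6, M8), because Table 1 gives suspected-only patients no other samples. Comparison C can be tested at up to 8. Five points are named as pre-treatment (1, 2, 3, 6, 8). Planned numbers are 160 confirmed and 90 not confirmed.

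**Assumed inputs.** The transmural share is not given; 80 patients are assumed. The correlation of a marker's test statistics between time points is not given; 0 to 0.9 is used.

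**1. Chance that a null marker passes**

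With k independent tests, P(pass) = 1 − 0.95^k:

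- k = 4: 1 − 0.8145 = 18.5%
- k = 5: 1 − 0.7738 = 22.6%
- k = 8: 1 − 0.6634 = 33.7%

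With equal correlation between points (simulation, 500,000 draws of z-statistics, limit 1.96):

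| Correlation | 4 points (A, B) | 5 pre-treatment points | 8 points (C) |
|---|---|---|---|
| 0 | 18.5% | 22.6% | 33.7% |
| 0.5 | 15.5% | 18.3% | 25.1% |
| 0.8 | 11.5% | 12.8% | 15.7% |
| 0.9 | 9.4% | 10.2% | 11.9% |

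If correlation instead decays with distance (first-order autoregressive, 0.5 between neighbours), the rates are 16.5%, 20.1% and 29.9%. The overall range is about 9 to 34%. Creatinine, troponin, white cell count and CRP are scheduled at only three points, for which 1 − 0.95^3 = 14.3%.

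**2. Upward bias among markers that pass** (Wilcoxon test, one time point, simulated)

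| True AUC | Patients | Passes | Mean AUC when it passes |
|---|---|---|---|
| 0.50 (null) | 80 vs 90 | 5% | 0.60 |
| 0.55 | 80 vs 90 | 21% | 0.61 |
| 0.60 | 80 vs 90 | 62% | 0.63 |
| 0.65 | 80 vs 90 | 92% | 0.66 |
| 0.50 (null) | 40 vs 45 | 6% | 0.65 |
| 0.50 (null) | 15 vs 20 | 4% | 0.73 |

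The bias is confined to weak markers and grows as groups shrink. For the null rows the AUC is taken in whichever direction exceeds 0.5.

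**3. What goes unreported**

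Under the null, SE(AUC) = √[(n1 + n0 + 1) / (12·n1·n0)].

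- 80 vs 90: √(171 / 86,400) = 0.0445, and 1.96 × 0.0445 = 0.087. An observed AUC between about 0.41 and 0.59 fails at that point.
- 15 vs 20: √(36 / 3,600) = 0.10, and 1.96 × 0.10 = 0.196. An observed AUC between about 0.30 and 0.70 fails at that point.

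A marker drops out only if it fails at every point.

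**4. Does the filter change the score?**

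- Null markers at the later gate: 0 of 3,000 reached LR+ > 5 with LR- < 0.2 at any group size tried (15 vs 20 up to 160 vs 90).
- A marker on the gate: sensitivity = specificity = 5/6 gives LR+ = (5/6)/(1/6) = 5 and LR- = (1/6)/(5/6) = 0.2. For binormal data this is an AUC of about 0.91. Such a marker has p < 0.05 in 96.7% of runs with 10 vs 10 patients, 99.9% with 15 vs 20, and 100% with 40 vs 45.

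The filter therefore protects the model from almost nothing that the gate does not already stop, and costs the model almost nothing.

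**The case against.** The strongest reply is that the objectives concern a combination of markers meeting likelihood-ratio limits, and step 4 shows that the filter barely touches that. This stands. A reader might infer that chance passes would contaminate the score or that useful markers would be lost from it; the plan's own later gate rules out both in practice.

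Second, a reader might infer that failing markers would have no accuracy result at all. The protocol does not establish this. The pooled AUROC is described for each marker, and every marker is described at every point whatever its p-value. But the text does not say whether failing markers enter the pooled step. A pooled figure also does not replace the time-point results, since success is defined at a time point.

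Third, tempting single figures go too far. A pass rate of 16 to 25% holds only for a correlation near 0.5 with 4 to 8 points. Saying that some null marker passes with probability 78% (A) or 92% (C) requires all nine central markers to be null and independent. Table 2 credits several with moderate accuracy and groups IL-6 with PCT as inflammatory markers. Nor does the protocol claim a 5% error rate; 0.05 is only a screening threshold.

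Fourth, the bias can be small. In a simulation of the any-point rule over four points (assumed 80 vs 90 at M1 shrinking to 20 vs 40 at M8, correlation 0.5), a true AUC of 0.55 is reported in 41% of studies and its M1 estimate then averages only 0.58. The 0.64 seen at the most significant point would matter only if that point alone were shown, which the plan does not say.

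Finally, full tables for null markers might be left to a document not shown. That does not excuse the rule, which is stated here as a condition for doing the analysis.

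**Conclusion.** The concern holds as a reporting defect. Followed as written, the plan withholds time-point accuracy estimates from markers that miss an unadjusted p < 0.05 everywhere, and overstates weak markers that pass (0.55 becoming about 0.61 at the point of passing, under the assumed 80 vs 90). The selectivity comes from leaving out the failing markers. The raised pass rate of null markers, about 9 to 34% depending on the number of points and the assumed correlation, is a secondary matter. Two further faults are in the text itself: comparison C can satisfy the filter on post-intervention samples, and the status of the pooled AUROC is unclear.

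The primary objective and the composition of the score are hardly affected. Because the filter also gives almost no benefit, there is no reason to keep it, and it should be removed.

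**What to change.** In the statistical analysis section:

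- Delete the p < 0.05 condition.
- State that AUROC with 95% CI, and sensitivity, specificity, predictive values and likelihood ratios at the chosen cut-off, will be reported for every biomarker in the List of biomarkers section, central and local, for each comparison. This covers each applicable pre-treatment point and the pooled data.
- State that the univariate p-values are descriptive and do not decide which markers go forward.

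The likelihood-ratio gate into the regression can stay as it is for this purpose. Naming pre-treatment points removes the mismatch in comparison C, and naming the pooled data removes the ambiguity there.

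Cost: a short rewording and a longer results table or supplement. No additional patients, samples or assays are needed.
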